#### Exclusion criteria

ALT/AST > 8 times the upper limit of normalPregnancy or breastfeedingKnown hypersensitivity to any study medicationAny medical condition which would impose an unacceptable safety hazard by participation in the studyStudy drug-specific exclusion criteria:For aprotinin
Known active thromboembolic disease (unprovoked venous thromboembolism (VTE), VTE in the last 3 months, myocardial infarction or coronary stenting in the last 6 months, ischemic stroke in the last 6 months)Renal insufficiency with creatinine clearance (CrCl) < 30 mL/min or renal replacement therapyFor high-prophylactic dose of LMWH
Active bleeding, a history of intracranial bleeding, or a recent (< 3 m) gastrointestinal (GI) bleeding requiring transfusion and/or intervention, recent surgery in the central nervous systemRenal insufficiency with CrCl < 20 mL/min or renal replacement therapyBlood platelet count < 30,000/μLIncreased risk of bleeding as judged by the investigatorNeed for therapeutic anticoagulation (known active thromboembolic diseases, atrial fibrillation, mechanical prosthetic heart valve…)Active bacterial endocarditisChronic alcoholismFor anakinra
Impairment of cardiac function defined as severe heart failure, unstable angina pectoris, myocardial infarction within 6 months before enrollment, ventricular arrhythmia requiring treatment or interventionSevere renal dysfunction (CrCl ≤ 20 mL/min) or renal replacement therapyUncontrolled hypertension (persistent SBP > 180 mmHg, or DBP > 110 mmHg)Clinical suspicion of latent tuberculosis or severe bacterial surinfectionKnown hypersensitivity to proteins produced by *E. coli*

### Who will take informed consent? {26a}

Potential participants are screened on the emergency ward or upon arrival at the COVID-ward. Accordingly, an emergency physician or a supervising physician at the COVID-ward who is trained in the protocol will first assess the patient’s interest in the study, if necessary through the legal representative. If there is an interest in participating, the investigators of the DAWn-study team again check the eligibility criteria and contact the patient or legal representative to provide more information and obtain informed consent. When signed informed consent is not permitted because of safety regulations related to the prevention of the transmission of SARS-CoV-2, the ethical committee approved the use of verbal informed consent. The consent form is read and illustrated by the investigator on the phone, and the patient or legal representative gives verbal consent which will be documented in the medical records, all in the presence of a witness. Signed informed consent shall then be obtained as soon as permitted based on safety regulations to prevent the transmission of SARS-CoV-2. The process for obtaining and documenting initial and continued informed consent from potential trial participants will be conducted following the International Conference on Harmonization of Technical Requirements for Registration of Pharmaceuticals for Human Use–Good Clinical Practice or ICH-GCP E6(R2), applicable regulatory requirements, and internal standard operating procedures (SOPs).

### Additional consent provisions for collection and use of participant data and biological specimens {26b}

Data can be reviewed by an audit group or Ethics Committee to verify the quality of the trial. Encoded trial data may be sent to other EU and non-EU countries for review by health authorities, Ethics Committee, external researchers, and the sponsor of the trial. The results of the trial will be used to answer the scientific questions of the trial. In addition, the sponsor can use the participant’s data obtained from this trial, in connection with other research and development activities. Any additional research outside of the trial must be approved by a Belgian recognized Ethics Committee.

Since scientific progress in this area is constant, the remainders of the patient’s biological samples will be kept for 30 years. The samples will be used for future research, to better understand the disease, its treatment and the responses to this treatment, and the admitted study drugs. Any future research, additional to what is described above, may only be conducted according to the legislation on the use of human tissue material and with the approval of a Belgian recognized Ethics Committee. As a general rule, the participant will be asked to sign an additional informed consent form in which the additional research is specified.

## Interventions

### Explanation for the choice of comparators {6b}

Following the guidelines of the Belgian Society on Thrombosis and Haemostasis and Sciensano, we use a higher than usual dose of thromboprophylaxis in the control arm [21]. ICU patients receive a dose of 50 IU anti-Xa/kg LMWH twice daily; ICU patients with a creatinine clearance below 30 mL/min and patients admitted to the wards receive a dose of 50 IU anti-Xa/kg LMWH once daily.

### Intervention description {11a}

Interventions (Fig. 2) consist of aprotinin on top of a higher dose of thromboprophylaxis. Anakinra will be added as soon as signs of hyperinflammation are observed.

#### Higher dose thromboprophylaxis

Patients randomized to the intervention arm will receive LMWH at 50 IU/kg (e.g., enoxaparin 0.5 mg/kg) twice daily, with a minimum of 4000 IU (e.g., 40 mg enoxaparin) twice daily, in non-ICU patients and 75 IU/kg (e.g., enoxaparin 0.75 mg/kg) twice daily—with a minimum of 4000 IU (e.g., enoxaparin 40 mg) twice daily—in ICU patients. The total daily dose will be reduced by 50% in patients with a CrCl < 30 mL/min (once daily instead of twice-daily administration). In patients who develop severe renal dysfunction (CrCl < 15 mL/min) or who require renal replacement therapy, the administration of LMWH should be interrupted until CrCl returns ≥30 mL/min. In patients who develop a CrCl < 15 mL/min, choice and dose of thromboprophylactic therapy is left to the discretion of the investigator. Options may include unfractionated heparin in a continuous IV infusion with a target activated partial thromboplastin time (aPTT) 40–60 s or a target anti-Xa of 0.2–0.4 U/mL, and with routine follow-up of aPTT or anti-Xa as per local practice. In patients receiving aprotinin (first 72 h), aPTT and ACT should not be used to monitor heparin effects, and the use of anti-Xa levels is suggested for heparin monitoring.

#### Aprotinin

Additionally, to suppress hyperfibrinolysis and the bradykinin-kallikrein pathway, patients will receive aprotinin. Aprotinin will be administered as an IV infusion of 2 MIE over 30 min four times per day from day 0 to day 3. Before the first administration, a test dose of 1 mL of a 50-mL vial will be given, with control of vital parameters for 20 min, before proceeding to full study dose. Administration of aprotinin will be at 6-h intervals, with the first administration together with the first administration of study LMWH. Further details on administration are disclosed in the full protocol affixed.

#### Treatment of hyperinflammation

Patients in the intervention arm will be monitored for hyperinflammation. If, at any point during the study, the patient develops signs of hyperinflammation, treatment with anakinra will be started if there are no contraindications (see the “Exclusion criteria” section).

Presence of hyperinflammation is defined as follows:
Absolute lymphocyte count < 1000 cells/mLTwo of the following: (i) ferritin > 800 ng/mL, (ii) LDH > 400 U/L, or (iii) D-dimers > 1000 ng/mL

These lab values have been identified as independent predictors of adverse outcome in patients with severe COVID-19 [2, 4, 22, 23].

Anakinra will be administered by IV infusion at a total dose of 400 mg per day, divided into 4 doses 100 mg IV every 6 h. Anakinra treatment will continue for 15 days, i.e., days 1 to 15. Before administration, the full content of the prefilled, single-use syringe (anakinra 100 mg) will be diluted in 100 mL saline. The IV administration of anakinra has to occur immediately after the preparation over an infusion period of 60 min. Full instructions for the preparation of anakinra are available in the IMP manual. Conditions for storage and injection are described in the attached protocol.

### Criteria for discontinuing or modifying allocated interventions {11b}

Circumstances requiring premature treatment interruption or discontinuation of the trial include but are not limited to (1) safety concerns related to IMP or unacceptable intolerability, (2) trial participation while in violation of the inclusion and/or exclusion criteria, (3) pregnancy or intention of becoming pregnant, (4) thrombotic complication, (5) bleeding complication, and (6) seizures. In patients receiving anakinra who develop ventricular arrhythmia requiring intervention, uncontrolled hypertension, or severe renal dysfunction or renal replacement therapy, anakinra infusion will be stopped.

In any such case of early trial termination and/or treatment interruption/discontinuation, the investigator will continue to monitor the participant’s condition closely and ensure adequate medical care and follow-up.

### Strategies to improve adherence to interventions {11c}

For each drug, SOPs were created. Detailed information on administration is provided within the hospital’s electronic system and is displayed when nurses administer the drugs. Permanent remote assistance is available as investigators are on standby 24 h a day, 7 days a week.

Investigators and clinical trial assistants (CTAs) will monitor drug administration daily. Remarks or problems with administration, which did not need telephonic assistance, can be marked via the electronic system. Per protocol, laboratory tests will be evaluated daily. Based on these assessments, some patients will be started on anakinra when criteria are met.

### Relevant concomitant care permitted or prohibited during the trial {11d}

There are currently no approved treatments for COVID-19. Patients will receive the standard of care as continuously updated by national and international guidance. Because the intervention of DAWn-AntiCo is independent of the background antiviral therapy, any antiviral therapy is allowed, including other investigational agents. Thus, concomitant participation in a study with antiviral agents does not exclude a patient from randomization within DAWn-AntiCo.

### Provisions for post-trial care {30}

As per European legislation, the sponsor has a full insurance that covers the costs of potential harms.

### Outcomes {12}

The study outcomes are based on the WHO master protocol, which has been proposed for all COVID-related research by the WHO [19, 20]. The ordinal scale below has also been used in multiple other COVID-19 studies [24, 25]. All outcomes will be presented overall as well as separately for patients with mild/moderate vs. severe disease at baseline.

Pilot phase of DAWn-Antico:

We will conduct a pilot phase with a pilot phase-specific primary endpoint analysis of D-dimer levels measured on day 6.

#### Primary outcome

The primary outcome is the time from day 0 to sustained clinical improvement or live discharge, whichever comes first, whereby a sustained clinical improvement is defined as an improvement of > 2 points vs. the highest value of days 0 and 1 and sustained for at least 3 days.

Clinical status of the subject at day 15 (on a 7-point ordinal scale):
Not hospitalized, no limitations on activitiesNot hospitalized, limitation on activitiesHospitalized, not requiring supplemental oxygenHospitalized, requiring supplemental oxygenHospitalized, on non-invasive ventilation or high flow oxygen devicesHospitalized, on invasive mechanical ventilation or extracorporeal membrane oxygenation (ECMO)Death

#### Secondary outcomes

Secondary outcomes include clinical outcomes and markers of thromboinflammation at predefined time points. A summary is listed below; the detailed list is provided in the full protocol attached.
Clinical status and time to clinical improvementMortality (day 15, day 28, time to death)Duration of supplemental oxygen, mechanical ventilation, hospitalization, ICU stay, time to live weaning, and time to live dischargeUsages and doses of rescue anti-inflammatory therapy (such as corticosteroids, IL-1 or IL-6 blockers—non-limitative)Adverse eventsStandard laboratory valuesMarkers of hyperinflammation (CRP, ferritin, LDH, interleukin profile)Markers of thrombotic activation and kallikrein-bradykinin activation (D-dimers, fibrinogen, PT, aPTT, C1-inhibitor, factor XII)Markers of adrenal function (cortisol, ACTH, albumin/transcortin)Combined cardiac endpoint during hospitalizationIncidence of thrombotic events and major bleeding complications during hospitalization as per ISTH criteria

### Overall long-term exploratory outcome

Five to 7 weeks post-discharge, patients are invited to the respiratory clinic for (lung) functional and radiological evaluation if possible.A telephone call will be done on D90 post-admission for survival status evaluation.

### Participant timeline {13}

A schedule of enrolment, interventions, assessments, and visits for participants is shown in Table 1.

**Table 1 Tab1:**
[figure not shown]
Participant timeline

### Sample size {14}

Sample size estimates provided serve as a reference, but not as an indication of the final number of patients to be randomized.

In the pilot phase of DAWn-AntiCo, we will evaluate the effect of modulation of the thromboinflammatory response on biochemical parameters. To evaluate the effect of this strategy, we will evaluate the difference in mean D-dimers on day 6. Published data show highly variable D-dimer values in patients with COVID [2, 3]. For an estimated mean D-dimer of 1000 with a standard deviation of 600, a sample size of 51 patients (17:34 with 1:2 randomization) has a power of 0.8 and an alpha of 0.05 to detect a difference of 500. We will therefore evaluate the effect of the intervention after a pilot phase of 60 (20:40) patients. Based on the information from other DAWn studies, the final sample size for effect on clinical outcomes will be evaluated following this pilot phase.

In their study comparing clinical improvement rates for lopinavir-ritonavir in hospitalized patients with severe COVID-19, Cao et al. reported a clinical improvement rate in the control group of 37.7% on day 14 [25].

Therefore, for our sample size calculations, we assume that a 40% improvement rate will be observed on day 15 in the control group, which yielded an expected hazard ratio of 1.5632. Since all missing clinical status data up to day 15 will be imputed, we assumed no censoring of the data prior to day 15. Based on the log-rank test, with a 2-sided significance level of 5% and 80% statistical power and using a (2:1) randomization ratio in favor of the intervention, we estimate that a total sample size of 354 patients will suffice to detect an absolute improvement of 15% (i.e., 55% in the intervention group). To detect an absolute improvement of 20% (60% in the intervention group), a total sample of 196 patients will suffice. We propose a pragmatic sample size of 210 patients taking into account early dropouts.

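### The sizes of 354 and 196 match an approximation that is optimistic at 2:1 allocation; the log-rank test has about 76% power there, not 80%, and 210 leaves essentially no room for dropout

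*Protocol article*

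**What the plan says.** All the figures are in the protocol article, Sample size {14}. For the clinical endpoint, "we assume that a 40% improvement rate will be observed on day 15 in the control group". A hazard ratio of 1.5632 is given, and no censoring before day 15 is assumed because missing clinical status is to be imputed. The basis is stated as "Based on the log-rank test", "with a 2-sided significance level of 5% and 80% statistical power", "using a (2:1) randomization ratio in favor of the intervention".

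Two sizes follow:
- for 55% in the intervention group, "a total sample size of 354 patients will suffice to detect an absolute improvement of 15" percentage points;
- for 60% in the intervention group, "a total sample of 196 patients will suffice".

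The section then concludes: "We propose a pragmatic sample size of 210 patients taking into account early dropouts". It names neither the sample size formula nor a dropout rate. It opens by describing its estimates as a reference rather than the final number, and says that the size for clinical outcomes will be evaluated after the pilot phase.

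**The concern.** The section makes a claim about the power of a named test under assumptions that are fully specified. Under proportional hazards these inputs determine the power: the log-rank test uses only the order of the event times, so the shape of the baseline hazard does not matter. The claim can therefore be checked directly.

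There was reason to check it. The Schoenfeld formula is a first-order approximation in the log hazard ratio. Here the hazard ratios are not small, and two thirds of the patients are in the arm that is expected to improve faster. In that configuration the formula credits each event with more information than it carries.

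Two things are at stake. One is whether 354 and 196 deliver the stated 80%. The other is whether the 14 patients between 196 and 210 (14/210 = 6.7%) are a true allowance for dropout or are already needed to reach the target.

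**Working it through.** **Inputs (Sample size {14}).** Two-sided alpha 0.05, power 0.80, share in intervention 2/3, control improvement 40% by day 15, intervention 55% or 60%, no censoring before day 15.

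**Hazard ratios.** HR = ln(1 − p_int)/ln(1 − p_con).
- 15 points: ln(0.45)/ln(0.60) = 1.5632, as stated.
- 20 points: ln(0.40)/ln(0.60) = 1.7937 (derived; the section does not give it).

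**Reproducing the plan's figures.** Schoenfeld events: d = (1.960 + 0.842)² / [(2/3)(1/3)(ln HR)²], with numerator 7.849.
- 15 points: 7.849/(0.2222 × 0.1996) = 177 events. Overall event probability (0.40 + 2 × 0.55)/3 = 0.500. N = 177/0.500 = 354, exactly as stated.
- 20 points: 7.849/(0.2222 × 0.3414) = 103.5, rounded up to 104 events. Overall event probability (0.40 + 2 × 0.60)/3 = 0.5333. N = 104/0.5333 = 195, against 196 stated.

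By this formula the power is 80.0% at 354, 80.4% at 196, and 83.0% at 210 for the 20-point effect.

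**Why the formula is optimistic here.** With share p of the risk set in the intervention arm, an event falls in that arm with probability q = p·HR/(1 − p + p·HR). The log-rank statistic gains q − p per event; Schoenfeld replaces this by p(1 − p)·ln HR.
- 2:1, HR 1.5632: q = 0.7577, so q − p = 0.0910, against 0.2222 × 0.4467 = 0.0993. The true gain is 92% of the assumed one.
- 2:1, HR 1.7937: q = 0.7820, so q − p = 0.1153, against 0.2222 × 0.5843 = 0.1298, or 89%.
- 1:1, HR 1.5632: q = 0.6099, so q − p = 0.1099, against 0.25 × 0.4467 = 0.1117, or 98%.

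These are values at the start of follow-up. As intervention patients improve and leave the risk set, it drifts back towards balance: by day 15 the intervention share in the 15-point case is 2 × 0.45/(2 × 0.45 + 0.60) = 0.60. Part of the loss is recovered. The Freedman formula, which takes no account of that drift, asks for too many (421 and 246). The truth lies between the two formulas.

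**Simulated log-rank power.** Proportional hazards, follow-up ending at day 15, two-sided 5%, 40,000 trials per case (simulation standard error about 0.2 points).

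| Total (control:intervention) | Effect | Stated | Schoenfeld | Simulated |
|---|---|---|---|---|
| 354 (118:236) | 40% v 55% | 80% | 80.0% | 76.7% |
| 196 (65:131) | 40% v 60% | 80% | 80.4% | 75.7% |
| 210 (70:140) | 40% v 60% | not stated | 83.0% | 79.0% |
| 210 (70:140) | 40% v 55% | not stated | 57.8% | 53.2% |

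Simulated type I error was about 5%. Separate runs agreed within about one point. Tying event times to whole days gave 76.8%, 76.6% and 79.4% for the first three rows; a Cox Wald test gave 76.6%, 75.4% and 78.6%.

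**Size for 80%.** By simulation, about 384 patients for 15 points (79.8%) and about 217 for 20 points (216 gave 79.9%).

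**Control check.** Schoenfeld's own 1:1 sizes, 332 and 184, gave simulated power of 80.0% and 79.6%. The shortfall therefore belongs to this 2:1 configuration and is not a preference for one formula over another.

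**Dropout at 210.** About 217 complete patients are needed for 80% at 20 points, so 210 is already slightly short. If 10 patients contributed nothing (an illustration, since no rate is stated), 200 would remain, with simulated power of 77.0%.

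**The case against.** The strongest reply is that the figures reproduce with a standard, widely used formula and consistent inputs. That stands. A reader might infer an arithmetic slip; the documents do not support it, and what is left is the inaccuracy of an approximation.

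A reader might also infer that 210 is clearly underpowered for the 20-point effect. It is not: about 79% is one point short, which is small beside the uncertainty in the assumed 40% control rate. Nor is the low power for 15 points concealed, since the same section says that effect needs 354. Missing clinical status is to be imputed (Methods {20c}), so dropouts are not wholly lost. What survives is narrower: the margin that 210 is said to contain is essentially absent.

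A third inference would be that the trial's real power is 76%. The documents do not support that either. The primary analysis in Statistical methods {20a} is a Fine and Gray model adjusted for baseline clinical status, with death as a competing risk. Adjustment for a prognostic baseline could move power by an amount comparable to the gap. The 76% describes the log-rank sizing claim only.

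Finally, the section calls its figures a reference and defers the final size until after the pilot. That limits the consequence. It does not make the stated power correct, and these figures are the natural starting point for the later evaluation.

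**Conclusion.** The point holds as a minor correction to a stated figure. Under the section's own assumptions, the log-rank test has about 76 to 77% power at 354 and about 76% at 196, a shortfall of roughly 3 to 4 points from the stated 80%. At 210 it has about 79% for 20 points and about 53% for 15 points, before any dropout.

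The result rests on proportional hazards, 2:1 allocation in favour of the intervention, complete follow-up to day 15, and the 40% control rate. It does not depend on the baseline hazard shape, and whole-day ties or a Cox Wald test change it little.

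**What to change.** In Sample size {14}:

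1. State the power under the log-rank sizing assumptions: about 76% at 354 (40% v 55%) and at 196 (40% v 60%); at 210, about 79% for 20 points and about 53% for 15 points, before dropout.
2. Remove the implication that 210 contains a dropout reserve, or give an assumed dropout rate and quote the power that remains after it.
3. When the size is re-evaluated after the pilot, confirm it by simulation at 2:1, preferably with the planned Fine and Gray analysis, so that the same optimism is not carried into the final number.

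The cost is a few sentences and a short simulation. No extra patients are required; the stated power becomes slightly less favourable.

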### Recruitment {15}

All patients diagnosed with COVID-19 are screened at the emergency ward or upon arrival at the COVID-ward. Accordingly, an emergency physician or a supervising physician at the COVID-ward that is trained in the protocol will first assess the patient’s interest in the study, if necessary through the legal representative. If there is an interest in participating, the investigators of the DAWn-study team again check the eligibility criteria and contact the patient or legal representative to provide more information and obtain informed consent. Therefore, every hospitalized patient with COVID-19 is screened upon hospitalization.

